## Abstract

**Background:**

Older people in poor health are more likely to need extra money, aids and adaptations to allow them to remain independent and cope with ill health, yet in the UK many do not claim the welfare benefits to which they are entitled. Welfare rights advice interventions lead to greater welfare income, but have not been rigorously evaluated for health benefits. This study will evaluate the effects on health and well-being of a domiciliary welfare rights advice service provided by local government or voluntary organisations in North East England for independent living, socio-economically disadvantaged older people (aged ≥60 yrs), recruited from general (primary care) practices.

**Methods/Design:**

The study is a pragmatic, individually randomised, single blinded, wait-list controlled trial of welfare rights advice versus usual care, with embedded economic and qualitative process evaluations. The qualitative study will examine whether the intervention is delivered as intended; explore responses to the intervention and examine reasons for the trial findings; and explore the potential for translation of the intervention into routine policy and practice. The primary outcome is the effect on health-related quality of life, measured using the CASP 19 questionnaire. Volunteer men and women aged ≥60 years (1/household) will be identified from general practice patient registers. Patients in nursing homes or hospitals at the time of recruitment will be excluded. General practice populations will be recruited from disadvantaged areas of North East England, including urban, rural and semi-rural areas, with no previous access to targeted welfare rights advice services delivered to primary care patients. A minimum of 750 participants will be randomised to intervention and control arms in a 1:1 ratio.

**Discussion:**

Achieving a trial design that is both ethical and acceptable to potential participants, required methodological compromises. The choice of follow-up length required a trade-off between sufficient time to demonstrate health impact and the need to allow the control group access to the intervention as early as possible. The study will have implications for fundamental understanding of social inequalities and how to tackle them, and provides a model for similar evaluations of health-orientated social interventions. If the health benefits of this intervention are proven, targeted welfare rights advice services should be extended to ensure widespread provision for older people and other vulnerable groups.

**Current Controlled Trials ISRCTN Number:**

ISRCTN37380518

## Background

### Socio-economic inequalities in health, income and older people

Health inequalities are universal across nations, societies and the human lifecourse [1-3]. Socio-economic differences in health persist into old age and social inequalities in self-reported physical and mental health widen in early old age [4]. The poorest older people have inadequate access to services essential to health and well-being [5]. Older people, especially those in poor health, are more likely to require additional income and support, including payments for care, domestic help and aids and adaptations to the home [6-8].

### Resource-based interventions to promote health

The vast body of evidence on socio-economic inequalities in health suggests a close relationship between access to resources and health status. Increasing an individual's or group's access to material, social or financial resources should result in improved health [9,10], yet little research has directly evaluated the impact of increasing resources on health [11]. A systematic review of ten North American randomised controlled trials of income supplementation experiments targeting a range of age groups, carried out in the late 1960s and 1970s, showed that none had reliably assessed the effects of increased income on health. The authors pointed out that, although such experiments are unlikely to be repeated, one way of assessing the health impact of increasing financial resources on health lies with assisting claimants to obtain full welfare benefit entitlements [11]. Tackling health inequalities has become a major policy priority for the UK government, highlighted, for example, in the white paper on public health (‘Saving Lives: Our Healthier Nation’). Following publication of the ‘Acheson Report’ [2] and the advent of Health Action Zones (HAZs) in the late 1990s [12], there was an increase in welfare rights advice projects linked to primary care in the UK. A voluntary organisation estimated in 2000 that there were >130 welfare rights advice services targeting primary care patients in England [13]. In 1999, 'Reducing Health Inequalities: an Action Report' [14], highlighted welfare rights advice as a potentially effective intervention to reduce health inequalities. This proposal was endorsed by the UK Government’s ‘Marmot Review’ in 2012 [3].

### Social welfare for older people and under-claiming of entitlement

In the UK, large amounts of social welfare benefits go unclaimed [15,16], and a disproportionate amount of these are the health-related benefit entitlements of vulnerable groups, such as older people [17,18]. Failure to claim entitlements is linked to a number of factors including the complexity of the benefits system [19], lack of knowledge about entitlements and difficulty in making claims [8,20-22]. In addition to the state pension, there are a number of means-tested and non-means-tested benefits that can be awarded if entitlement conditions are fulfilled. The level of under-claiming varies depending on the benefit concerned, but is estimated to be at least 30 % for the main benefits [23]. Entitlement to one benefit can often act as a ‘passport’ to others, since many of the benefits aimed at people over national retirement age are linked together in a complex network of entitlements that are often difficult for people to access without expert assistance.

### Welfare rights advice services and their evaluation

Our systematic review of the health, social and economic impacts of welfare rights advice services in healthcare setting [21], identified numerous studies that have demonstrated the financial and material benefits of such services. Welfare rights advice provided by local authorities, charities and voluntary organisations is known to increase uptake of benefits, particularly where this involves ‘active assistance’ with benefit claims [2,17]. Studies have also shown that receipt of benefit entitlements can be increased by providing information and advice in general practice, particularly in relation to those benefits that are health-related [24-28]. However, our systematic review only identified two studies that have investigated the health impact of welfare rights advice; [29-31] one of which found an improvement in health-related quality of life in some of the subscales of the SF36 [29,30]. However, both studies demonstrate the difficulties of identifying and measuring appropriate health outcome measures when assessing the health effects of welfare rights advice in primary care [29-31]. Neither study used a randomised controlled design, and both suffered from significant methodological weaknesses that render them inconclusive. Qualitative studies exploring the impact of welfare rights advice on clients in primary care identified a range of health-related outcomes that can potentially result from receipt of welfare rights advice, including changes in physical, behavioural and, in particular, psycho-social domains of health [8,20-22].

We conducted a pilot randomised controlled trial (RCT) to prepare for the definitive RCT described here, evaluating the impact of a domiciliary welfare rights advice service offered to people aged ≥60 years, identified via primary care in disadvantaged areas [7,8,32]. This pilot trial increased uptake of financial (median gain £55/week) and non-financial benefits (e.g. aids and adaptations to the home) in 58 % of participants [7], confirming the feasibility and success of the intervention from the point of view of accessing unclaimed benefits. It also provided vital information on the feasibility of such a trial, which has helped in planning the current definitive RCT.

Welfare rights (WR) advice interventions lead to greater income, but have not been rigorously evaluated for health benefits, in part because such research has previously been deemed unethical [33]. We present the protocol for a definitive RCT of WR Advice for people aged ≥60 years, and discuss the methodological and ethical issues that needed to be taken into account in designing the trial. We identified challenges relating to: randomisation, contamination, equipoise and control condition, length of follow-up, selection bias, outcome measures, generalisability and nature of the intervention. These are analysed in relation to scientific and ethical considerations.

## Objectives

The proposed RCT with embedded economic and qualitative process evaluations aims to answer the following questions:

1. What are the effects on health-related quality of life of a domiciliary welfare rights advice service targeting independent-living, socio-economically disadvantaged older people (aged ≥60 yrs) identified via primary care?

2. What are the cost consequences and what is the cost-effectiveness of a domiciliary welfare rights advice service targeting independent-living older people (aged ≥60 yrs) identified via primary care?

3. What is the acceptability to trial participants and relevant professionals of a domiciliary welfare rights advice service targeting independent-living older people (aged ≥60 yrs) identified via primary care?

4. What are the unanticipated consequences (positive or negative) of a domiciliary welfare rights advice service targeting independent-living older people (aged ≥60 yrs) identified via primary care?

### Study Design

The study is a pragmatic, individually randomised, single blinded, wait-list controlled trial of welfare rights advice versus usual care, with embedded economic and qualitative process evaluations. The qualitative study will examine whether the intervention is delivered as intended, explore responses to the intervention and examine reasons for the trial findings, and explore feasibility of the translation of the intervention into routine policy and practice. The trial design is illustrated in Figure 1, which has been drawn according to the CONSORT guidelines [34].

**Figure 1 F1:**
[figure not shown]
CONSORT 2010 standard RCT flow diagram for Do-Well study (numbers, where they appear, are estimates at this stage).

### Primary outcome measure

The primary outcome is quality of life, measured using the CASP 19 questionnaire which was developed for use with older people [35,36]. CASP stands for the four domains of Control, Autonomy, Self realization and Pleasure. CASP 19 will be administered by face-to-face interview at baseline (pre-randomisation) and at follow-up 24 months post-randomisation, and by postal questionnaire at 12 months post-randomisation.

### Secondary outcome measures

The following secondary outcomes, based on the findings of previous research, including our own systematic review, qualitative study and pilot trial [7,8,20-22,32,37] will be collected:

· *Health status*, measured by the EuroQoL (EQ5D) [38]

· *Functional ability* measured by the modified Townsend activities of daily living scale [39]

· *Independence* categorised as: living independently or with carer support, in own home, with relations, care home or hospital (the latter two categories at follow-up only)

· *Mental health* measured by the PHQ-9 depression questionnaire [40-42]

· *Health-related behaviours* assessed by self-report to measure change in key indicator behaviours, such as smoking, alcohol consumption, diet (consumption of key food groups) and physical activity, as in our pilot RCT [7]

· *Mortality* assessed by identifying deaths at 12 months and 24 months from GP records (we will do this prior to commencing follow-up assessments, so as not to attempt to contact the recently deceased, which may cause distress to bereaved relations)

· *Social support and participation* measured by the Social Support Questionnaire [43].

· *Perceived financial wellbeing* measured by the Affordability Index [44].

· *Fuel poverty* measured where a household can achieve temperatures needed to maintain health and comfort for expenditure of less than 10 % of income [45]

· *Financial status* measured by a standard assessment tool developed and used in our pilot RCT [7]. This includes data on all sources of household income, including benefits, major outgoings (rent/mortgage, fuel bills etc.), debts and capital assets (i.e. home and savings). As well as these data, at follow-up detailed data will be collected (by WR Advisors) on new benefits received since baseline, including one-off (lump sum) payments and regular, weekly or monthly income.

· *Material (dis)advantage* measured through standard questions to ascertain home ownership, size of home (number of ‘living’ rooms), car ownership, and access to household amenities (such as central heating, cooker, fridge, freezer, etc.).

These outcomes will be assessed by structured, face-to-face interview at baseline (pre-randomisation) and 24 months post-randomisation.

### Other quantitative data to be collected

As well as demographic factors including age, sex, ethnicity, marital status and living arrangements, including dependants, data will be collected to assess the costs of the intervention, from public sector and treasury perspectives (see ‘Health economic analyses’ below). The service costs of delivering the intervention will be assessed by collecting data on staff salaries from all participating services, as well as data on typical caseloads. WR Advisors routinely record information on visits to clients and we will use these data to estimate time spent with study clients, as well as travel costs. These data will be used to derive an average cost per case of delivering the intervention to our intervention group participants, as in our pilot RCT [7]. To assess the treasury perspective, total gains in financial benefits for all intervention clients will be provided by WR Advisors. We will also estimate the cost to the treasury of non-financial benefits based on details of successful claims provided by WR Advisors. These costs will then be summed to derive average costs to the treasury per case for all intervention participants.

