#### Comparator (wait-list control condition)

Participants randomised to the control group will receive ‘usual care’ from both health and social services after randomisation until they have completed their 24-month follow-up assessment. They will be given no advice regarding welfare rights as a part of the study intervention during this period. However, they may independently seek welfare rights advice from the local authority, CAB or voluntary sector organisations. If this occurs, they will remain in the trial, but details of such advice and ensuing claims and outcomes will be recorded at the 24 months follow-up assessment. Following their 24-month follow-up assessment, they will receive the intervention, as delivered to the intervention group (described above), including all follow-up visits by WR Advisors and assistance with claims and appeals over the following months, until all claims have been resolved.

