#### Health economic analyses

The economic evaluation will consist of a cost analysis conducted from the perspectives of public sector services (‘Do-Well’ service delivery costs), and that of the Treasury (total cost of additional benefits paid out). The mean change in benefits and the mean change in total income of participants will also be calculated.

The cost analyses above will be used in conjunction with study outcomes to produce a cost consequences analysis [49]. If any significant change in EQ-5D health utility scores can be attributed to the intervention, we will undertake a cost-utility analysis [49]. The assumptions that underpin any such cost-utility analysis will be subjected to one-way sensitivity analysis [50] and, in addition, extensive probabilistic sensitivity analysis [50] will be used with results presented in the form of cost-effectiveness acceptability curves [50].

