### Generalisability

Our pilot trial was undertaken in one social services district (Newcastle upon Tyne) and in 4 general practice populations [7]. However, we know, from other work and discussions locally, that service delivery in welfare rights advice varies from area to area, as do general practice populations. To enhance the potential generalisability of the results, the RCT will therefore be undertaken across a range of geographical and local authority areas (including urban and rural) and general practices. It is possible, indeed likely, that the present welfare regime will change during the course of the trial. The proposed intervention is not dependent on any particular set of benefits and is adaptable to any new regime. This adds to its future generalisability.

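### The Treasury cost is built from intervention-arm gains only, so it is a gross figure and not the incremental cost that belongs beside the randomised outcomes

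*Protocol article*

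**What the plan says.** Other quantitative data to be collected describes the Treasury cost in three steps.

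- Financial benefits: "total gains in financial benefits for all intervention clients will be provided by WR Advisors".
- Non-financial benefits: "We will also estimate the cost to the treasury of non-financial benefits based on details of successful claims provided by WR Advisors".
- Summary: "These costs will then be summed to derive average costs to the treasury per case for all intervention participants".

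Health economic analyses names the Treasury perspective as the "total cost of additional benefits paid out" and does not say relative to what. It continues: "The mean change in benefits and the mean change in total income of participants will also be calculated". It then combines the cost analyses with the study outcomes in a cost-consequences analysis, and adds a cost-utility analysis if a significant EQ-5D change is attributed to the intervention.

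The outcomes are handled differently. Statistical analyses compares primary and secondary outcomes between arms at 24 months, by intention to treat and adjusted for baseline.

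Comparator (wait-list control condition) allows controls to look for advice on their own. They then stay in the trial, and "details of such advice and ensuing claims and outcomes will be recorded at the 24 months follow-up assessment". Equipoise and the control condition adds that self-referral and professional referral stay open to trial patients. Secondary outcome measures lists financial status, which covers benefit income, as an outcome. It also plans for advisors to collect data on new benefits at follow-up, without limiting this to one arm.

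**The concern.** Cost-effectiveness sets the extra cost of a service against its extra effect. Here the effect is a randomised difference, from which whatever would have happened anyway has been removed. The Treasury cost is a total from one arm, from which nothing has been removed. If some intervention participants would have obtained benefits over two years without the service, those payments are charged to the service.

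At stake is the second objective, on cost consequences and cost-effectiveness. A Treasury cost that is too high makes the service look dearer per unit of health gained, and the error passes into any acceptability curves. Since the article states how the figure is calculated, this is a choice already made and not a detail left to a fuller economic plan.

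**Working it through.** The document gives no Treasury cost, so there is no stated figure to reproduce. The check asks how far a gross figure can differ from an incremental one.

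**Inputs**

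- p = 58%: share of pilot participants with a gain (Welfare rights advice services and their evaluation). This counts financial and non-financial gains together.
- g = £55 per week: median pilot gain (same section), used here in place of a mean.
- T = 104 weeks, as if payment ran for the full 24 months. This is generous: under Length of follow-up, only 45% of pilot participants had their entitlements by 3 months.
- c: share of controls gaining over 24 months. The document does not give it, so a range is assumed.

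**Formulas** (same gain per recipient in both arms)

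- Gross cost per intervention participant = p × g × T
- Incremental cost per participant = (p − c) × g × T
- Excess = p/(p − c) − 1

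Gross = 0.58 × 55 × 104 = £3,318.

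| c (assumed) | Incremental cost | Excess of gross over incremental |
|---|---|---|
| 0% | £3,318 | 58/58 − 1 = 0% |
| 5% | 0.53 × 55 × 104 = £3,032 | 58/53 − 1 = 9.4% |
| 10% | 0.48 × 55 × 104 = £2,746 | 58/48 − 1 = 20.8% |
| 20% | 0.38 × 55 × 104 = £2,174 | 58/38 − 1 = 52.6% |

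The pound figures are illustrative only. The percentages depend on neither the £55 nor the 104 weeks, provided that amount and duration per recipient are equal in the two arms. If controls gain half as much per recipient, c is in effect halved: 10% of controls then gives the 9.4% row.

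**Direction.** Suppose advisor records miss gains that a share u of the intervention arm made without the advisor. The recorded figure is then proportional to p − u and the incremental one to p − c. The recorded figure is too high only if c exceeds u. That is the likelier case: every intervention participant is offered a full entitlement assessment within two weeks of randomisation, so most claims that would have come later by another route should pass through the advisor. It is not certain.

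**What the pilot says about c.** Study design, level of randomisation, contamination and dilution reports that no pilot control sought advice, over 6 months. Statistical analyses gives 126 pilot participants. Assuming an equal split, 0 of 63 has an upper 95% limit (two-sided, exact) of 1 − 0.025^(1/63) = 5.7%. So even for 6 months a rate of 5% is not excluded, and the trial runs for 24. The observation also concerns seeking advice, not benefits obtained without it.

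**The case against.** The best defence is that the section concerned is about data collection, that it never calls its figure incremental, and that gross outlay per case is a fair descriptive number for a Treasury reader. That stands, and the gross figure deserves to be reported. It does not settle the matter, because the economic section carries the cost analyses into comparisons with randomised outcomes and names no other Treasury cost for that purpose.

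A reader might infer more than the document supports, in four ways.

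- *That overstatement is established.* It is not. The excess is nil if no control gains, the only pilot evidence is zero advice-seeking, and advisor records could miss gains in the intervention arm. The article also says "It is possible, indeed likely, that the present welfare regime will change during the course of the trial", but this gives no direction and could lower benefits as well as raise them.
- *That the trial makes no comparison of finances between arms.* Financial status is a listed secondary outcome and falls under the planned between-arm analysis. That comparison is simply not named as the Treasury cost.
- *That the data source is known to differ by arm.* The text does not settle this. One section has advisors collecting new-benefit data at follow-up for unspecified participants, another has them supplying intervention clients' gains, and a third has controls' own claims recorded at the 24-month assessment.
- *That control data are missing.* They are planned, and this is why the correction is cheap.

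The planned mean changes in benefits and income do not close the gap. They are described for participants, with no contrast between arms, and as an addition to the Treasury cost.

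**Conclusion.** The point holds in a limited form. The Treasury cost as described is a one-arm gross figure and does not match the randomised contrast it is to be set beside. It will probably overstate the incremental cost. The size is unknown: 0% to 53% for assumed control gains of 0% to 20%, with equal gain per recipient and the pilot's 58%, which includes non-financial gains.

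This is a fault in how a quantity is defined, and no data are lost by it. It affects the cost-consequences analysis and, if it is done at all, the conditional cost-utility analysis. The CASP-19 analysis and the randomised secondary comparisons are unaffected. Severity is moderate.

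**What to change.** 1. For the cost-consequences and cost-utility analyses, define Treasury cost, change in benefits and change in total income as the intervention-minus-control difference per randomised participant over 24 months, by intention to treat.
2. Measure all three the same way in both arms, using the financial status tool given at baseline and 24 months together with the planned new-benefit data on lump sums and regular payments. The tool alone gives two snapshots of income and not the sum paid in between, so both are needed.
3. Report the advisor-recorded gain per intervention case separately, labelled as gross and descriptive.
4. Reconcile Secondary outcome measures, Other quantitative data to be collected, and Comparator (wait-list control condition) on who records new benefits in each arm and when.

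The cost is mainly a change of wording before the economic analysis, using data already planned. The downside is a Treasury figure that is probably smaller and certainly less precise, since it carries the sampling error of both arms.

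### The Treasury cost is a gross total from the intervention arm alone, so it is not the incremental cost of offering advice whenever controls also gain awards

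*Protocol article*

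**What the plan says.** Only the protocol article is at hand. Its section *Other quantitative data to be collected* gives the recipe for the Treasury perspective. On the financial side, "total gains in financial benefits for all intervention clients will be provided by WR Advisors". Non-financial awards are costed from the successful claims that the advisors report. Then "These costs will then be summed to derive average costs to the treasury per case for all intervention participants". Numerator and denominator both come from the intervention arm.

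*Health economic analyses* names two costing perspectives: service delivery, and "that of the Treasury (total cost of additional benefits paid out". It names no comparator for the second. It goes on: "The cost analyses above will be used in conjunction with study outcomes to produce a cost consequences analysis". A cost-utility analysis follows only if a significant EQ-5D change can be attributed to the intervention. The same section adds: "The mean change in benefits and the mean change in total income of participants will also be calculated".

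*Statistical analyses* compares primary and secondary outcomes between the arms at 24 months, adjusted for baseline and by intention to treat.

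*Comparator (wait-list control condition)* says of controls that "they may independently seek welfare rights advice from the local authority, CAB or voluntary sector organisations". Those who do so stay in the trial, and their advice, claims and results are recorded at 24 months.

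**The concern.** A cost-consequences table invites the reader to set what the advice costs against what it achieves. Here the effect column is a randomised contrast, and the Treasury column is a one-arm total. The total answers how much benefit advisors obtained for their clients. Objective 2, on cost consequences and cost-effectiveness, needs to know how much more the Treasury paid because advice was offered. The two answers agree only if the intervention arm would have gained nothing new without the offer.

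The control arm is the trial's evidence on that point, and the stated recipe does not use it. Awards that would have been made anyway are then charged to the advice. If a cost-utility analysis is triggered, the same figure could enter an incremental ratio.

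**Working it through.** **Is a control term subtracted anywhere?**

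| Quantity | Section | Contrast stated |
|---|---|---|
| Treasury cost | Other quantitative data to be collected | Intervention clients only, mean per intervention participant |
| Treasury cost | Health economic analyses | Additional benefits paid, no comparator named |
| CASP-19, EQ-5D, financial status | Secondary outcome measures; Statistical analyses | Intervention versus control, baseline-adjusted |
| Claims by controls | Comparator | Recorded at 24 months, not linked to the Treasury cost |

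No section subtracts a control figure from the Treasury cost.

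**Could controls gain awards?** The article leaves this open. They may seek advice themselves. *Equipoise and the control condition* keeps referral by professionals available. *Target Population* says that eligibility for health-related benefits rises with age. *Generalisability* adds: "It is possible, indeed likely, that the present welfare regime will change during the course of the trial". Against this, *Study design, level of randomisation, contamination and dilution* reports that no pilot control sought advice, over 6 months. That is a quarter of the 24-month wait (6/24 = 0.25), and it counts advice sought rather than awards received.

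**How large could the difference be?** The article states no Treasury cost, so there is no figure of its own to reproduce. What follows is an illustration.

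Inputs from *Welfare rights advice services and their evaluation* (pilot): a median gain of £55 a week, and 58 % of participants with financial or non-financial gains.

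Assumptions:
- the median stands in for the mean;
- all 58 % are financial gainers;
- control gainers receive the same amount for the same time;
- the control share c is what the intervention arm would have gained without the offer, and those awards lie inside the advisors' total;
- c ranges from 0 % to 20 %, which the article neither gives nor supports.

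Formulas:
- gross cost per participant per year = 52 × £55 × 0.58 = £2,860 × 0.58 = £1,659;
- incremental cost = £2,860 × (0.58 − c);
- overstatement = 0.58/(0.58 − c) − 1 = c/(0.58 − c).

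| Control share c | Incremental cost per year | Gross figure too high by |
|---|---|---|
| 0 % | £2,860 × 0.58 = £1,659 | 0 % |
| 5 % | £2,860 × 0.53 = £1,516 | 0.05/0.53 = 9 % |
| 10 % | £2,860 × 0.48 = £1,373 | 0.10/0.48 = 21 % |
| 20 % | £2,860 × 0.38 = £1,087 | 0.20/0.38 = 53 % |

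The £55 cancels from the percentages, so using a median as a mean affects only the pound figures. The 58 % does not cancel. If the share with financial gains is lower, a given c produces a larger percentage.

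**The case against.** The best defence is that the difference may be small or nil. The only control-arm evidence in the article is that no pilot control sought advice. The article also describes substantial under-claiming and services usually reached only on demand or by referral, so many advised claims might not otherwise have been made. The advisors' totals come from casework and may leave out awards that intervention participants obtained alone, which would reduce the overstatement. All of this stands as a limit on size. It does not turn a one-arm total into an incremental cost.

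It can also be said that a cost-consequences analysis only lists costs beside outcomes, that any ratio is conditional, and that the primary outcome is untouched. That stands too, and it lowers the severity.

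Three stronger readings are tempting, and the article does not support them:
- A reader might infer that the mean change in benefits and income is an uncontrolled before-after figure that absorbs yearly uprating. The sentence names no arm and no contrast. Financial status, which includes household income and benefits, is a secondary outcome at baseline and 24 months, and *Statistical analyses* compares secondary outcomes between arms. A randomised income comparison is therefore already planned.
- A reader might infer from the word for gains that reduced or stopped benefits are ignored. The article does not say so, and the financial-status tool would show lower benefit income in either arm.
- A reader might infer that the financial-status tool could simply replace the advisors' data. It may miss lump sums and non-financial awards, which the present recipe can include.

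**Conclusion.** The concern holds for the Treasury cost. As written, it is the gross gain of the intervention arm with no control term, set beside outcomes that are between-arm differences. It equals the incremental cost only if the advisors' total contains nothing that would have been awarded without the offer.

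The size cannot be established from the article. The illustrated overstatement of 0 % to 53 % rests on an assumed control share of 0 % to 20 % and on the simplifications listed in the working. It shows sensitivity and is not an estimate.

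The service delivery cost is not at fault. Controls receive no study advice before 24 months, so counting it in the intervention arm is correct.

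Severity is moderate: one of two costing perspectives under a secondary objective is affected, and the primary analysis is not.

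**What to change.** In *Other quantitative data to be collected* and *Health economic analyses*, define the Treasury cost used in the cost-consequences analysis and any cost-utility analysis as the intention-to-treat difference between arms in new benefits since baseline, up to the 24-month assessment, with a confidence interval.

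- **Sources:** use the new-benefit and financial-status data under *Secondary outcome measures* together with the control claims recorded under *Comparator*. State that new-benefit data are collected in both arms on one definition.
- **Valuation:** value lump-sum and non-financial awards the same way in both arms.
- **Mean change:** say that the change in benefits and in total income is the baseline-adjusted difference between arms.
- **Advisors' total:** keep the gross intervention-arm figure and label it descriptive.

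The cost is a change of wording and some extra analysis on data that the article already plans to collect. The Treasury estimate will carry a wider confidence interval than a one-arm total, and control-arm awards will rest partly on participants' own reports, which should be acknowledged when the result is presented.
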